
#### Secondary outcome

*Pain knowledge and beliefs*. Adolescents’ knowledge of and beliefs about pain will be measured in adolescents with and without chronic pain using the Concept of Pain Inventory in German (COPI- GER). The COPI- GER was initially designed for children and adolescents aged 8 to 12 years and assesses a child’s concept of pain and therefore their beliefs and knowledge of pain [31]. Children indicate their level of agreement with 14 statements using a 5-point Likert scale (‘Fully agree, ‘agree’, ‘unsure’, ‘disagree’ or ‘Do not agree at all’). Scores range from 0 to 56 with higher scores indicating greater alignment with contemporary pain science knowledge. The COPI may identify potential misconceptions in a child’s concept of pain and thereby facilitating the individualized targeting of pain science education [31]. In a content validation process conducted with 13 experts, the "Item-based content validity index" (I-CVI) ranged from 0.85 to 1.00, while the "Scale-based content validity index" (S-CVI) yielded an acceptable score of 0.93 [52]. The construct validity was confirmed by good goodness-of-fit indexes. Specifically, the Normed Fit Index, Incremental Fit Index, and Comparative Fit Index were all above 0.90, while the Root Mean Square Error of Approximation was less than 0.08 [32]. The total Cronbach’s alpha was 0.78 [31,32], indicating good reliability. Validation of the German version is currently underway.

*Exploratory outcomes*. We will explore for any associations and correlations between the presence/absence of chronic pain, the impact of pain and adolescents’ knowledge and beliefs about pain.

### Statistical analysis plan

Data will be entered, cleaned, and analysed using the Statistical Packages for the Social Sciences (SPSS), currently version 27. An estimate of the point prevalence of chronic pain will be reported, with a 95% confidence interval. Adolescents’ demographics, pain characteristics, PROMIS-PPIS and COPI-GER scores will be reported for the entire cohort and according to presence/absence of chronic pain, age and gender using standard descriptive statistics. Continuous data will be reported using mean scores, ranges, and standard deviations. Logistic regression models will be constructed to first establish the association between the presence of chronic pain, including PROMIS-PPIS and demographic factors (age, gender). Next the relationship between chronic pain and total COPI-GER score as well as individual items in the child’s COPI-GER, independent of age and gender, will be explored with logistic regression models. Results will be expressed as odds ratios.

Linear regression models will be used to explore the association between the pain interference (PROMIS-PPIS) and the pain knowledge and beliefs (COPI-GER) in adolescents with and without chronic pain, with further analysis by age and gender. Sensitivity analyses will be performed to assess the robustness of the results, such as excluding participants or outliers.

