### Data collection

The PI (HS) will be present in the classroom together with the teacher to administer the link to the questionnaires or reading substitute task to all adolescents. This also ensures that direct enquiries can be made and compliance with the study protocol. Excluded children adolescents receive help from HS and the teacher to decide on the substitute task. Participating adolescents will be invited to complete questionnaires related to i) their demographics (age, gender, class grade), ii) the absence/presence of chronic pain, iii) pain characteristics and impact (those with chronic pain only), and iv) knowledge and beliefs about pain. The demographic data and the pain-related questionnaires will be completed via the cloud-based survey tool LimeSurvey. Piloting the questionnaires ensured that the questions were comprehensible and took approximately ten minutes to answer.

During the data collection period anonymised data will be stored digitally in the LimeSurvey cloud and will be accessible to the research team only. After each data collection session the data will be exported to and stored in a password protected folder on the Haute École de Santé Vaud in Switzerland for ten years. All data will be handled in accordance with current Swiss legislation [36]. On completion of the study we will make our anonymised data available without restriction on the Open Science Framework [35].

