#### Primary outcomes

The IASP defines chronic pain as “pain that persists or recurs for longer than 3 months” [37]. For the purpose of this study, we operationally defined the presence of chronic pain as the self-reported experience of recurrent or persistent pain for three or more months and a frequency of at least weekly [38–42]. This definition was chosen because it is the most commonly used and can therefore be compared with other studies from the field [9,12].

The presence/absence of chronic pain will be determined by participants’ self-reported responses to the following two questions:

“Chronic pain is defined as pain that is recurrent or persistent for 3 months or longer. Do you feel chronic pain?” Response options: “No, I don’t feel chronic pain”, “Yes, I have felt pain that has lasted 3 months or longer.”“How often do you feel this pain?” Response options: “daily”; “weekly”; “monthly”, or “rarely” [38,40,41].

Those adolescents with chronic pain according to the operational definition will be invited to provide self-report additional information in order to characterise their pain, including:

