The location and total number of sites of their chronic pain, assessed via two body charts. The body chart is divided into 11 specific locations (head, neck, chest, shoulders, back, arms, hands, bottom/hips, belly/pelvis, legs, and feet) and an “other” category. For the first body chart, the child will be asked to mark the region in which they feel their most bothersome chronic pain. A second body chart will assess the number of chronic pain sites by the question: “Are there other areas where you have felt pain for 3 month or longer”. The chronic pain sites have a score range from 0 to 12 based on axis I of the IASP Classification of Chronic Pain [43] and has been used in previous studies investigating pain in adolescents [5,40,44]. Its reliability and validity are unknown.Usual pain intensity by asking, “How intense the pain feels usually?”, using an 11-point Numerical Rating Scale (NRS-11) (0 = no pain to 10 = the worst pain you can imagine”. This question provides a generic pain intensity and does not distinguish between pain at rest or activity [45]. The NRS-11 has been shown to provide reliable and valid scores when used with adolescents to assess current pain [46]. A high level of agreement in pain intensity ratings between the first and second measurements (Limits of Agreement: -0.9 to 1.2, 95% CI), indicating good reliability [46]. The NRS-11 has good convergent validity showing moderate to high correlations with other pain intensity scales [46]. Discriminant validity was supported by moderate correlations with measures of pain unpleasantness (r = 0.63) and functional impairment (r range: 0.35 to 0.43). The NRS-11 has demonstrated moderate correlations with measures of disability (r range: 0.22 to 0.39), psychological well-being (r range: 0.46 to 0.66), and pain interference (r = 0.62) [46]. Threshold values have been identified. Average scores of 3, 6, and 8 on the NRS-11 correspond to mild, moderate, and severe pain levels, respectively [46]. The NRS-11 has been used in a number of pain-related pediatric epidemiological studies [40–42].Pain duration by asking:” For how long have you felt this pain?”, with the response options: “3–6 months”, “6–12 months”, “1–2 years” or “over 2 years”. The validity and reliability of this retrospective question in adolescents is unknown. It has been used in numerous studies in adolescents [41,47–49] and will facilitate comparisons of results.The impact of their pain using the Patient Reported Outcome Measures Information System—Pediatric Pain Interference Scale (PROMIS-PPIS) short version in German [50]. PROMIS-PPI assesses self reported impairments in physical, psychological, and social functioning. The PROMIS-PPIS is an 8-item questionnaire studied in chronic pain children and adolescents, aged 2–17 years old. Scores range from 0 to 32 with higher scores indicating greater pain-related functional impairment. The PROMIS-PPIS is reliable [50] and has good internal consistency [51].

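### PROMIS-PPIS is collected only from pupils with chronic pain, but secondary and exploratory analyses use it as if pupils without chronic pain also had a score

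*Protocol article*

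**What the plan says.** **Who receives the scale.** The Data collection section lists the questionnaire blocks and limits the third: "iii) pain characteristics and impact (those with chronic pain only"). The Primary outcomes section gives the same rule: "Those adolescents with chronic pain according to the operational definition will be invited to provide self-report additional information". PROMIS-PPIS is one of the items that follow, introduced as "The impact of their pain using the Patient Reported Outcome Measures Information System". By contrast, the Secondary outcome section says that knowledge and beliefs "will be measured in adolescents with and without chronic pain using the Concept of Pain Inventory in German". Nowhere does the protocol give PROMIS-PPIS to pupils without chronic pain or assign them a value.

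**How the scale is used.** The Statistical analysis plan section names three uses:

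- Descriptive: "PROMIS-PPIS and COPI-GER scores will be reported for the entire cohort and according to presence/absence of chronic pain, age and gender".
- Logistic: "Logistic regression models will be constructed to first establish the association between the presence of chronic pain, including PROMIS-PPIS and demographic factors (age, gender").
- Linear: models for the association between "the pain interference (PROMIS-PPIS) and the pain knowledge and beliefs (COPI-GER) in adolescents with and without chronic pain".

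**Missing values.** The Missing data section gives, as an example of when to impute, an outcome measure missing in 10% or more of participants, with chained equations as the method.

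**The concern.** The collection rule and the analysis rule do not fit together. A variable that exists only where chronic pain is present cannot help to explain whether it is present, and it cannot be compared between pupils with and without it.

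Two things could follow. An analyst working on complete records finds an empty comparison group and must change the model after seeing the data. An analyst who counts the absent scores as ordinary missing data passes the 10% threshold and imputes them. The models then run and return estimates for pupils without chronic pain that rest on no observation from that group. The second outcome is the worse one, because nothing in the output would show it.

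**Working it through.** **Inputs.** The Sample size section gives 288 responses, an assumed prevalence of 25%, precision of 5 points, a response rate of 80%, a target of 360, a population of 86424, and earlier prevalence estimates of 3% to 38%. The collection rule comes from the Data collection and Primary outcomes sections.

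**1. The plan's own figure.** n = z²p(1−p)/d² = 1.96² × 0.25 × 0.75 / 0.05² = 288.1, or 287.2 with the finite population correction 288.1 / (1 + 287.1/86424). Inflating for response, 288 / 0.8 = 360. Both stated figures reproduce. They concern prevalence only and are not in question.

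**2. Pupils with a PROMIS-PPIS score.**

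| Prevalence | With score (all cases) | Without score, by design | Share without |
|---|---|---|---|
| 3% | 288 × 0.03 ≈ 9 | 279 | 97% |
| 25% (plan) | 288 × 0.25 = 72 | 216 | 75% |
| 38% | 288 × 0.38 ≈ 109 | 179 | 62% |

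**3. Logistic model, read as presence of chronic pain on PROMIS-PPIS, age and gender.** The complete records are the 72 scored pupils, and the outcome equals 1 in each. With no non-cases, no odds ratio exists. A trial fit on simulated data obeying the collection rule (288 pupils, 72 cases) failed with perfect prediction. Setting the score to 0 for pupils without chronic pain does not help: if every case scores at least 1, separation is complete and the fit also fails. These failures do not depend on sample size.

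**4. Linear model across both groups.** Take the terms as intercept, COPI-GER, group, and group × COPI-GER. Among complete records group is always 1, so the group column equals the intercept and the interaction column equals COPI-GER. The design has rank 2 of 4, so neither the group difference nor the interaction is identified. Fitted separately, the model for pupils without chronic pain has n = 0.

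**5. Imputation.** Absence of 75% (62% to 97% over the quoted range) is far above the 10% threshold. No pupil without chronic pain has an observed score, so the data cannot inform the distribution of scores in that group or how it relates to COPI-GER. Imputed values would be carried over entirely from cases.

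**6. What remains estimable.** Prevalence (n = 288); chronic pain on age and gender (n = 288); chronic pain on COPI-GER (n = 288); PROMIS-PPIS on COPI-GER among cases (n about 72).

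**The case against.** **These are not the primary analyses.** This stands. The Abstract and the Aims and objectives section place the associations under secondary analyses, and the Secondary outcome section lists them as exploratory. The primary objectives are prevalence, and the characteristics and impact of chronic pain in those who have it. A reader might infer that the study's main results are at risk; the documents do not support that.

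**The logistic sentence is unclear.** This stands in part. Its wording leaves the second term of the association open, refers to models in the plural and fixes no covariate set. It could mean that PROMIS-PPIS is itself related to age and gender among cases. That could be estimated, though not as a logistic model of presence. The logistic part of this point therefore depends on the reading; the linear part does not, because the text names both groups.

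**The descriptive sentence can be read variable by variable.** This is fair. Each measure may simply be tabulated where it exists, and empty cells would mislead nobody. This is the weakest of the three conflicts.

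**The age and gender odds ratios survive.** A reader might infer that they are lost with the non-cases. That happens only if all terms share one model and incomplete records are dropped, which the protocol does not say. A model on age and gender alone can use all pupils.

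**The missing-data section does not order imputation outright.** This is correct. It first weighs a complete records analysis and an assumption of missing at random. But it does not separate values absent by design from values a pupil failed to give, so the 10% example could still be applied to them.

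**Conclusion.** The contradiction is real and lies within the current text, so it is not a detail that a fuller analysis plan could simply supply. At 288 responses and 25% prevalence, about 72 pupils have a PROMIS-PPIS score and 216 have none by design. The linear analysis in pupils without chronic pain has no data. On the most natural reading of its sentence, the logistic model has no non-cases among complete records.

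A reader might go further and say that these analyses can never be run. The documents do not support that either: under the 10% rule they could run, on scores extrapolated from cases, and that result should not be relied on.

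The conclusion assumes that the collection rule is applied as written. The counts depend on the assumed prevalence; the absence of scored non-cases does not.

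**What to change.** Before analysis begins:

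1. Model presence of chronic pain on age and gender, without PROMIS-PPIS.
2. Restrict the linear model of PROMIS-PPIS and COPI-GER, adjusted for age and gender, to pupils with chronic pain (about 72).
3. Restrict all summaries of PROMIS-PPIS and of pain characteristics to the same pupils, and drop their breakdown by presence or absence of chronic pain.
4. State in the Missing data section that values absent by design are not counted towards the 10% threshold and are not imputed.
5. Align the Data collection, Primary outcomes, Statistical analysis plan and Missing data sections, and report the change as a deviation, as the Limitations section promises.

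The cost is rewording and needs no new data. The price in content is that no comparison of interference between pupils with and without chronic pain will be available. Giving the scale to all pupils in the remaining sessions is not advised. Collection began in September 2023, so this would change the instrument mid-study and discard earlier sessions for that comparison. The number of pupils still to be surveyed is not stated.

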#### Missing data

Missing data will be handled according to the framework described by Lee et al. [53]. The number/proportion of missing values for each variable will be reported, along with any assumptions made regarding the cause of missingness. Patterns of missing data and likely reasons will be explored. The validity of a complete records analysis will be considered. If a complete records analysis is deemed invalid and the assumption is made that data are ’missing at random’, multiple imputation will be considered to reduce bias and improve precision. For instance, if data for a given outcome measure are missing from ≥10% of participants, missing data will be imputed using the multiple imputation by chained equations method [54]. The number of imputations will be determined based on the percentages of missing values, and the results for the imputations will be pooled using Rubin’s rule.

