#### Sample size

Previous studies have estimated that 3–38% of adolescents suffer from chronic pain. Assuming that 25% of our sample have chronic pain, this suggests that for a total of 288 responses, 95% confidence limits will be 20% and 30% with a precision of 5% (Sample size for prevalence surveys, © 2003–2005 Philippe Glaziou). With an estimated response rate of 80%, it is aimed to include 360 adolescents. The calculation is based on a population size of 86424 adolescents between 11 and 17 years in central part of Switzerland (canton Luzern, Aargau, Schwyz and Zug) in 2021.

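### The 10% imputation example does not separate items never asked from items missing, so for pain interference and pain characteristics its threshold is met by design

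*Protocol article*

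**What the plan says.** The Missing data section first commits to reporting missing values with their assumed causes. It adds: "Patterns of missing data and likely reasons will be explored". It then sets a condition: "If a complete records analysis is deemed invalid and the assumption is made that data are ’missing at random’, multiple imputation will be considered". The next sentence, introduced as an example of that condition, gives a percentage rule: "if data for a given outcome measure are missing from ≥10% of participants, missing data will be imputed", by chained equations with pooling by Rubin's rule.

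Two other sections fix who is asked what. Data collection lists "pain characteristics and impact (those with chronic pain only" as one part of the questionnaire. Primary outcomes says: "Those adolescents with chronic pain according to the operational definition will be invited to provide self-report additional information". The items that follow are pain sites, usual intensity, duration and PROMIS-PPIS. COPI-GER goes to pupils with and without chronic pain.

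The Statistical analysis plan section nevertheless plans pain characteristics and PROMIS-PPIS for the whole cohort and by chronic-pain status. It appears to place PROMIS-PPIS in a logistic model for the presence of chronic pain. It also plans a linear model of PROMIS-PPIS and COPI-GER in pupils with and without chronic pain.

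**The concern.** The percentage rule counts over participants and does not exclude items that a pupil was never routed to. For every pain variable restricted to chronic pain, the blanks created by routing alone pass 10%, so the threshold cannot tell a well-completed measure from a badly completed one.

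The two sentences also rest on different grounds. One makes imputation something to consider, depending on validity and mechanism. The other says that it will be done, depending on a percentage. A percentage establishes neither that complete records are invalid nor that data are missing at random.

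The impact of chronic pain is part of a primary objective. If scores were imputed for pupils never asked, the pooled output would look like an ordinary valid result.

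**Working it through.** **1. The plan's own figures (Sample size).** Inputs: prevalence p = 0.25, precision d = 0.05, 95% confidence, population N = 86424, response rate 80%.
- n0 = 1.96² × 0.25 × 0.75 / 0.05² = 288.1
- With finite population correction: 288.1 / (1 + 287.1/86424) = 287.2, rounded up to 288
- 288 / 0.80 = 360
- Limits: 0.25 ± 1.96 × √(0.25 × 0.75 / 288) = 20.0% and 30.0%

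All reproduce, so 288 and 25% are used below.

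**2. Share not asked by design.** This is 1 − p. The section states "Assuming that 25% of our sample have chronic pain" and also "Previous studies have estimated that 3–38% of adolescents suffer from chronic pain".

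| Prevalence | Asked, of 288 | Not asked, of 288 | Share not asked |
|---|---|---|---|
| 3% | 8.6 | 279.4 | 97% |
| 25% | 72 | 216 | 75% |
| 38% | 109.4 | 178.6 | 62% |

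The share is at least 10% at any prevalence up to 90%.

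**3. What the denominator does to the rule at 25% prevalence.**
- All participants, routed-out items counted as missing: 216/288 = 75% before any pupil leaves an item blank, so one genuinely lost score would fall under the rule.
- All participants, routed-out items not counted: 10% of 288 is 28.8, so 29 lost scores are needed, which is 29/72 = 40% of the pupils asked.
- Pupils meeting the definition: 10% of 72 is 7.2, so 8 lost scores are needed. Over the cited range this is 1 score at 3% (10% of 8.64 is 0.86) and 11 at 38% (10% of 109.44 is 10.9).

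The text does not say which of these applies.

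**4. Whether the conditional sentence prevents the problem.**
- Complete records: every pupil with a PROMIS-PPIS score has chronic pain. A logistic model for chronic pain that includes PROMIS-PPIS then has a constant outcome and cannot be fitted. An analyst could easily judge complete records inadequate.
- Missing at random: routing depends only on the answers to the two chronic-pain questions, which are observed, so the formal definition appears to be met. What fails is overlap. No score exists for any pupil without chronic pain, so chronic-pain status cannot inform the imputation model.

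**5. Direction and size if such scores were imputed.** Let mC be the mean score with chronic pain and mN the mean that pupils without it would have given. The true cohort mean is p·mC + (1 − p)·mN. An imputation model fitted only to pupils with chronic pain returns about mC for everyone if the covariates are similar in the two groups. The error is then about (1 − p)(mC − mN), or 0.75 points per point of true difference at 25% prevalence (0.62 to 0.97 over the cited range).

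The documents give neither mean. Purely as an assumption, mC = 14 and mN = 3 would give 0.75 × 11 = 8.25 points on the 0 to 32 scale, with a range of 0.62 × 11 = 6.8 to 0.97 × 11 = 10.7.

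Given the imputation covariates, the imputed scores carry no difference by chronic-pain status, so that association tends to null whatever the truth.

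**The case against.** A reader might infer that the rule fires automatically and that the plan will make up scores for three quarters of the pupils. The document does not support that. The 10% sentence is an example under a condition that requires an invalid complete-records analysis and missing at random, and it comes after causes and patterns of missingness have been examined. A questionnaire skip is a known cause, and an item never put to a pupil is not ordinarily called missing. No sentence says that scores will be imputed for pupils without chronic pain. This stands, and it limits the point to an ambiguity that can mislead.

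The distorted mean and association also need the whole-cohort PROMIS-PPIS analyses. If those were confined to pupils with chronic pain, values imputed for others would not enter them. This stands too, but the denominator would remain undefined (step 3).

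The size rests on assumed scores. A null association holds only conditionally: if age, gender or COPI-GER predict interference and differ by pain status, the imputed groups will differ somewhat. Both are accepted.

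It may be said that not-applicable codes and item denominators belong in a fuller analysis plan. That would answer a complaint of missing detail. Here, though, the article states a rule with its own denominator, and the planned whole-cohort results have no source in the document other than imputation.

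**Conclusion.** The point holds as an ambiguity with a real route to a wrong result, and should be corrected before analysis. With all participants as denominator, the 10% threshold is met by design for PROMIS-PPIS, intensity, duration and sites: 75% at the assumed prevalence and 62% to 97% over the cited range. These shares follow from the document's own figures.

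The conditions placed before the rule mean that imputation is not automatic. They do not reliably prevent it, because complete records cannot support the planned PROMIS-PPIS models and the missingness is formally explained by observed answers.

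The harm arises only if the rule is read literally together with the whole-cohort analyses. Its direction is clear, and its size depends on scores that the documents do not give. The prevalence estimate and COPI-GER are asked of everyone and are not affected by the routing.

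**What to change.** In Missing data:
- State that items skipped by routing are not applicable, and are neither counted as missing nor imputed.
- Compute percent missing for PROMIS-PPIS and the pain characteristics among pupils meeting the chronic-pain definition (about 72 of 288 at 25% prevalence, so 10% is reached at 8 scores), and impute these variables only within that group.
- Reword the 10% sentence so that the figure prompts an assessment and imputation follows only if complete records are judged invalid and missing at random is plausible. This also reconciles the two verbs.

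In Statistical analysis plan:
- Restrict PROMIS-PPIS and pain-characteristic summaries and models to pupils with chronic pain. Remove PROMIS-PPIS from any model whose outcome is the presence of chronic pain.

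The cost is a few sentences in two sections. The questionnaire, the sample size and the prevalence analysis do not change. The whole-cohort PROMIS-PPIS results are given up, but the data collected cannot support them.
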